### 8- Data analysis method

#### 8-1. The analysis of this observational study will be purely descriptive.

The demographic, clinical and radiographic qualitative variables will be described by their number, percentage and missing data by response modality and the quantitative criteria by their number, average, standard deviation. In the case of quantitative criteria with asymmetrical behavior, they will be presented with their median and the interquartile range (25th percentile - 75th percentile).

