#### 8-2. The endpoint is the response to treatment.

The aim of the study being the search **for predictive factors of response to treatment**, it is not relevant to determine a primary endpoint. We will study the possible correlation between the response to the treatment and the level of pain on D0, the duration of the symptoms, the presence of a limitation of the mouth opening, and the existence of radiological lesions of osteoarthritis on the panoramic dental picture.

[figure not shown]

The response to the treatment will therefore be estimated by 3 complementary methods and for each of them the predictive factors of response (YES/NO) will be studied. Each patient will be classified into a treatment response category: YES or NO depending on:

1. The patient's assessment of the effectiveness (effective and very effective = YES, not or only slightly effective = NO),
2. Reduction in pain of at least 3 points or at least 50% on the Likert scale.
3. The degree of patient satisfaction (Very satisfied and fairly satisfied = YES, little or not satisfied = NO),

We will look for predictive factors of response or non-response, first in univariate analysis then in multivariate analysis by integrating all the factors with a  $P < 0.1$  in the univariate analysis, as well as possible confounding factors such as age, gender, taking NSAIDs, wearing a tray.

The main analysis will be carried out on the per-protocol population including only patients for whom all the data at D0 and D180 are available, then confirmed by ITT. For patients who do not have D180 data, the latest data available (D90) will be used (LOCF). The regression coefficients of the multivariate models (ANCOVA and mixed model) will be considered significant if the degrees of significance are less than 5%. Statistical analyzes will be performed with XLStat software.

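### Section 8-2 tests four predictors against three equal-ranking responses at an unadjusted 5% in about 40 patients, although 8-1 promises a descriptive analysis: roughly a 30–54% chance of at least one false 'significant' predictor

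*Protocol*

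**What the plan says.** Protocol 8-1 opens with "The analysis of this observational study will be purely descriptive". Section 8-2 then sets out an inferential procedure:

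- **Outcome.** Because the aim is to find predictors, "it is not relevant to determine a primary endpoint". Instead, response is defined in three ways and the predictor search is run separately for each. The three definitions are the patient's rating of effectiveness, a fall in pain of a set size, and satisfaction.
- **Candidates.** Four factors are named: baseline pain, symptom duration, restricted mouth opening and osteoarthritic changes on the radiograph.
- **Selection.** Factors are examined "first in univariate analysis then in multivariate analysis by integrating all the factors" that pass P<0.1. Confounders enter in addition: "as well as possible confounding factors such as age, gender, taking NSAIDs, wearing a tray".
- **Decision rule.** Coefficients "will be considered significant if the degrees of significance are less than 5" per cent. The models named are ANCOVA and a mixed model, although each response is YES/NO. No adjustment for multiple tests is stated.

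Section 7 plans 44 inclusions to obtain 40 complete files. Section 8-3 calls the study exploratory, gives no power or precision calculation, and describes the purpose as raising hypotheses.

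**The concern.** Looking for predictors does not remove the need to say which outcome is being predicted. With three outcomes of equal standing, the predictor search is run three times, and any coefficient below 5% in any run counts as a finding. The number of chances to be wrong is the number of predictors times the number of definitions, while the error rate is held at 5% for each coefficient only.

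The P<0.1 screen raises a different problem. The data that let a factor into the final model are the data that then test it, so its final P value and effect size cannot be taken at face value.

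Predictors are the study's sole stated aim (section 1), and the results are meant for congresses and a peer-reviewed journal (6-2). Spurious or exaggerated predictors would therefore affect the main product of the study. A significance verdict also does not belong in an analysis that 8-1 calls descriptive.

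**Working it through.** **The plan's own figure.** Section 7: 40 complete files with 10% loss. 40 × 1.10 = 44, as stated; 40 / 0.90 = 44.4, i.e. 45. The difference is immaterial, and n = 40 is used below.

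**Number of tests (8-2).** 4 named predictors × 3 definitions = 12, each at 5% (two-sided assumed; 8-2 does not say).

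**Benchmark if the tests were independent.**
- Three definitions: 1 − 0.95^12 = 46.0%.
- One definition: 1 − 0.95^4 = 18.5%.
- Radiographic confirmation is an inclusion requirement (section 2), so that factor may hardly vary. With three usable predictors: 1 − 0.95^9 = 37%.

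**Simulation of the procedure with no true predictor.** n = 40; four candidates (two continuous, two binary, mutually independent); four confounders always in the model; three correlated YES/NO responses; screen at P<0.1; final model judged at 5%; 1,500 runs per setting. The protocol gives neither the correlation between definitions nor the response rate. Latent correlations of 0 to 0.9 and response rates of 50% and 70% are therefore assumptions.

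Chance of at least one false predictor among the four candidates, over three definitions (range over the two response rates):

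| Correlation | ANCOVA | Logistic, Wald | Logistic, likelihood ratio |
|---|---|---|---|
| 0 | 40% | 36–41% | 52–54% |
| 0.5 | 40% | 37–40% | 51–53% |
| 0.7 | 37–38% | 34–38% | 49–51% |
| 0.9 | 31–33% | 30–33% | 42% |

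The overall range is about 30–54%. For one definition it is 15–17% (ANCOVA) or 21–23% (logistic likelihood ratio).

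**What the screen does.** A separate ANCOVA simulation compared the procedure with and without it:
- three definitions: 30–41% with the screen, 32–43% without;
- one definition: 16–18% with, 17–19% without.

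So the screen does not raise the overall rate. Its effect is on the factors it keeps. A null P value is uniform, so half of those below 0.10 are also below 0.05 (0.05 / 0.10 = 50%). After the confounders are added, simulation gives about 44%, against the nominal 5%. The figures agree with each other: per definition, 4 × 0.10 = 0.4 null factors pass on average, and 0.4 × 0.44 = 0.18 reach significance.

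**Model size.** The largest model has 4 predictors + 4 named confounders = 8 coefficients. The smaller response class has at most 20 of 40 patients: 20 / 8 = 2.5 per coefficient. At an assumed 70% response it has 12: 12 / 8 = 1.5.

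**The case against.** The best defence is that the study is openly exploratory (8-3). No confirmatory claim hangs on the 5% rule, and unadjusted testing is a legitimate way to raise hypotheses. All three definitions are stated in advance and all three are to be analysed, so a reader who infers that the sponsor may pick whichever outcome works goes beyond the text. Model detail may also sit in a statistical analysis plan that is not shown.

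This lowers the stakes but does not remove the point. The 5% rule, the screen and the absence of a main definition are fixed in the protocol, so a later plan would have to overrule the protocol to repair them. An exploratory aim is a reason to leave out a significance verdict, not a reason to include one.

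Four stronger readings are tempting and not supported:

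- **That the screen or the confounders cause the inflation.** Without the screen the overall rate is the same or slightly higher. The confounders matter mainly through small-sample error in the logistic likelihood-ratio test.
- **That one exact error rate can be quoted.** The protocol gives no correlation or response rate. Effectiveness and satisfaction are two self-ratings by the same patient at the same visits (3-2), so high correlation, and hence the low end of the range, is plausible. ANCOVA, which 8-2 names, gave 31–40% in the table; figures above 41% come only from the logistic likelihood-ratio test.
- **That every model would have eight terms.** That needs all four candidates to pass. With no true predictor about 0.4 pass, so four or five terms is typical. The confounder list is also given as examples, so four is a reading of it.
- **That significant confounders count as false predictors too.** The chance would then be about 50–66% (ANCOVA and Wald), but 8-2 lists them as confounders, not as candidates.

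**Conclusion.** The point holds in this form. Section 8-2 attaches a 5% significance rule to 12 unadjusted tests in about 40 patients, with no main response definition, and this contradicts 8-1. If no predictor is real, the chance of at least one false 'significant' predictor is roughly 30–54%, against about 15–23% for a single definition. The range rests on assumed correlations of 0 to 0.9 between definitions, response rates of 50% and 70%, mutually independent predictors, and the choice among three tests. The multiplicity comes from three definitions times four predictors.

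Separately, the same-data screen makes the reported P values and effect sizes of retained factors unreliable: about 44% of null factors that pass it go on to reach P<0.05. In the worst case, with all four candidates retained, at most 2.5 patients in the smaller class support each coefficient. The protocol should be changed, but the study's exploratory purpose is not undermined.

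**What to change.** In 8-2:

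- Name one main response definition at D180 and call the other two supportive.
- Drop the P<0.1 screen. Fit one pre-specified model suited to a binary response, with the four named predictors and a closed list of chosen confounders. Without the screen every candidate stays in, so with all four confounders the eight-coefficient model becomes the rule. Penalised logistic regression is one suitable option for that reason, and a shorter confounder list would also help.
- Report odds ratios with 95% confidence intervals, labelled exploratory, and delete the 5% significance rule.

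In 8-1, describe the work as a descriptive and exploratory association analysis, so that the two sections agree.

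The changes do different jobs. One main definition cuts the number of main comparisons from 12 to 4; dropping the screen removes the selection bias and does not lower the overall rate. Anyone who reads the four intervals as tests would still face a chance of the order of 18.5% (the independent benchmark), which is why they should be presented as estimates.

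The cost is wording and analysis only, with no extra patients or visits. The downside is that individual predictors can no longer be reported as 'significant'.

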#### 3-1. During the selection visit (D0), the following elements will be collected:

- Demographics (gender, age, height, weight)
- Length of pain
- The target side

[figure not shown]

- Previous treatments for the pathology evaluated (NSAIDs, analgesics, muscle relaxants, infiltration of corticosteroids into the painful TMJ, injections of hyaluronic acid into the painful TMJ, specific rehabilitation of the oral sphere, wearing an occlusal splint)
- The search for bruxism, noises and / or crackles during chewing,
- TMJ pain on chewing measured on an 11-point numerical scale, "0" meaning "no pain" and "10" meaning "intolerable pain" (Likert 0-10),
- TMJ pain on palpation (Likert 0-10),
- The inter-incisor distance (IID) at the maximum opening of the mouth, measured in millimeters using a caliper.

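### Section 8-2 defines YES/NO responses but names only ANCOVA and a mixed model, and describes no outcome that those models would serve

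*Protocol*

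**What the plan says.** Protocol section 8-2 makes response to treatment the endpoint and states: "Each patient will be classified into a treatment response category: YES or NO". There are three definitions: the patient's rating of effectiveness, a fall in pain of 3 points or 50%, and the patient's satisfaction. Predictors are sought for each definition, first one at a time and then jointly.

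The same section then says of the joint step: "The regression coefficients of the multivariate models (ANCOVA and mixed model) will be considered significant" when the p-value is under 5%. These are the only multivariate models named in the protocol.

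The main analysis uses patients with complete D0 and D180 data. D90 enters section 8-2 only as the value carried forward when D180 is missing. Sections 3 and 4 describe a single-centre study.

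Sections 3-1 and 3-2 show what lies behind the YES/NO classes. Pain on chewing and pain on palpation are each scored 0-10 at D0, D90 and D180. Effectiveness and satisfaction are 4-point ratings at D90 and D180.

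**The concern.** Finding predictors of success or failure is the stated aim (sections 1 and 8-2), and the joint models supply its inferential result. ANCOVA, and a mixed model in its usual linear form, are models for a measured outcome. Section 8-2 gives one binary class per patient per definition and describes no repeated outcome. An analyst following it must therefore fit a linear model to 0/1 data, depart from the protocol, or switch to the continuous pain score. The text does not say which, so the choice could be made after results are seen.

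A second, smaller matter is that the scales for which ANCOVA and a mixed model are suited are already collected, but they are analysed only after being cut in two. With 40 patients that loss of information is worth limiting.

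**Working it through.** **The plan's own figure.** The protocol gives no power, effect size or responder rate. Its one derivable figure is recruitment: 40 × 1.10 = 44, as section 7 states (dividing instead, 40 / 0.90 = 44.4, or 45). This point does not depend on it.

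**Outcome against model.**

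| Item in section 8-2 | What it is | What the named models need |
|---|---|---|
| Effectiveness, pain and satisfaction responses | YES/NO | ANCOVA: a measured outcome |
| Time point | D180, with D90 only if D180 is missing | Mixed model: repeated or clustered outcomes |
| Centres | One | No centre effect to model |

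**What happens if ANCOVA is fitted to 0/1 data.** Simulation with 40 patients, one normal predictor, a normal outcome cut to give the stated responder share, and 2000 runs per setting. The responder shares and the correlation of 0.4 are assumptions.

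| Responders | Type I error: linear on 0/1 | Type I error: logistic (likelihood ratio) | Power: continuous | Power: linear on 0/1 | Power: logistic | Runs with a fitted value outside 0-1 (correlation 0.4) |
|---|---|---|---|---|---|---|
| 50% | 5.3% | 5.9% | 75% | 54% | 56% | 33% |
| 70% | 5.4% | 6.4% | 74% | 48% | 51% | 51% |
| 80% | 5.5% | 6.3% | 75% | 42% | 45% | 64% |

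Monte Carlo error at 5% is √(0.05 × 0.95 / 2000) = 0.5 percentage points. A repeat of the type I error check with another seed gave 5.1-6.3% for the linear model with one predictor and 4.9-5.5% with six. The linear model therefore keeps its error rate and loses only 2-3 points of power to logistic regression, whose own error rate runs slightly higher here. What suffers is interpretation: the coefficients are risk differences on a straight line that can leave the 0-1 range.

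**Information lost by the cut, pain score.** For a roughly normal score with responder share p, the share of information kept is φ(z_p)² / [p(1−p)].

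- p = 0.5: 0.399² / 0.25 = 0.637, loss 36%
- p = 0.7: 0.348² / 0.21 = 0.576, loss 42%
- p = 0.8: 0.280² / 0.16 = 0.490, loss 51%

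**Information lost by the cut, 4-point ratings.** Against a proportional-odds analysis of the same four categories, the share kept is [1 − p³ − (1−p)³] / [1 − Σp_k³].

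- Equal categories: 0.75 / 0.9375 = 0.80, loss 20%
- Shares 0.1, 0.4, 0.4, 0.1: 0.75 / 0.87 = 0.862, loss 14%
- Shares 0.1, 0.15, 0.35, 0.4: 0.5625 / 0.88875 = 0.633, loss 37%

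Under a latent normal scale, the splits tried gave losses of 26-35%, inside the same range.

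**Why a penalised fit.** Section 8-2 lists four candidate predictors and four confounders, so up to eight terms may enter. With 40 patients and 80% responders there are 40 × 0.2 = 8 non-responders; with 50% there are 20 in each class. Ordinary logistic regression can break down through separation at such counts.

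**The case against.** The strongest reply is that the harm is small where the protocol uses the models. Section 8-2 uses the coefficients only to call significance at 5%, and the simulation shows those calls barely change. That stands, and it limits the severity. The study is also described as exploratory in section 8-3 and has no primary endpoint.

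Several stronger readings are tempting, but the documents do not support them.

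- A reader might infer that the mixed model cannot be fitted at all. Section 3-2 collects all three response measures at both D90 and D180, so a logistic mixed model over the two visits is possible. It is undescribed, not impossible.
- A reader might infer that cutting the scores always discards a fixed share of the information, and might multiply the losses for pain and mouth opening. The familiar median-cut figure needs a normal score and a known split. Two of the three definitions rest on 4-point ratings. The pain rule depends on baseline: below a D0 score of 6, the 50% limb is the easier one to meet. No mouth-opening cut-off is given from which to compute a loss.
- A reader might infer that responder endpoints are themselves an error. The aim in section 1 is to predict success or failure, and section 8-2 fixes the response definitions in advance. Preferring continuous outcomes is a choice, not a correction.
- A reader might treat the missing threshold for "the presence of a limitation of the mouth opening" as a defect. A statistical analysis plan, not shown here, could supply it.

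The reply does not remove the mismatch. The protocol could have left the model to a later plan. Instead it named models that do not fit the outcome it defines.

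**Conclusion.** Wrong as written, and should be fixed. Section 8-2 pairs three YES/NO responses with ANCOVA and a mixed model, and describes no continuous or repeated outcome for either.

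The cost is in interpretability and in an analysis choice left open, not in false positives: type I error stays near 5%. Under the assumed correlation of 0.4 and 50-80% responders, about 33-64% of simulated runs produce a fitted probability outside 0-1.

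Information loss from dichotomising can be given only as a range under assumptions, since the protocol states no responder rate: about 36-51% for a roughly normal pain score at 50-80% responders, and about 14-37% for the 4-point ratings over the category splits tried. That loss supports adding a continuous analysis; it does not invalidate the responder analysis.

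**What to change.** In section 8-2:

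1. Analyse each YES/NO response by logistic regression, reporting odds ratios with 95% confidence intervals. A penalised fit such as Firth's suits 40 patients; other penalties would also serve.
2. Assign ANCOVA at D180, or a mixed model over D90 and D180, to the 0-10 pain score adjusted for D0 pain, as a stated supporting analysis. Say whether chewing or palpation pain is meant, because both are recorded.
3. Optionally, enter mouth opening at D0 as a continuous term in millimetres. Section 3-1 already collects it: "The inter-incisor distance (IID) at the maximum opening of the mouth, measured in millimeters using a caliper". This avoids the need for a cut-off.

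The cost is a few sentences in section 8-2 and a little more analysis. There are no new visits, measurements or patients. Before the method is fixed, the sponsor should check that the chosen software offers a penalised logistic fit. A result per millimetre is slightly less simple to present than limitation present or absent.

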### **8-3. Justification of the number of subjects**

The study being purely exploratory, the number of subjects required is not possible to determine a priori. A number of 40 patients was therefore chosen by the study's scientific committee, as likely to provide sufficient information to allow hypotheses to be put forward on the question posed while allowing reasonable feasibility.

[figure not shown]

## **9- Modalities for stopping the study**

### **9-1. Early termination of the study by a patient**

A patient who has agreed to participate in the study may at any time decide to stop participating without any obligation to provide explanations.

11

### **9-2. Early termination of the study by the investigator in the interest of a patient**

The investigator can at any time decide to stop the study in the interest of a patient.

### **9-3. Early termination at the promoter's instigation**

The sponsor reserves the right to interrupt the study at any time for medical or administrative reasons, if possible after consultation with the coordinating investigator, the study committees and the competent administrative authorities. In this event, an information letter will also be sent to the investigators. The reasons for the stop should be documented there.

## **10-Vigilance and management of adverse events**

As this study is observational and falls within current practice, it is not mandatory to include a section for collecting adverse events.

Nevertheless, the scientific committee and the sponsor wanted a collection as careful as in the interventional studies to be carried out.

### **10-1 Collection of adverse events by the investigators**

- Collection of non-serious adverse events: Investigators must note all adverse events, even non-serious, on the adverse event form in the observation notebook.
- Reporting of serious adverse events: In the event of a serious adverse event, the investigator has the obligation to report it without delay to the

[figure not shown]

promoter who immediately sends it to the distributor (Laboratoire Labrha) who himself informs the manufacturer of the medical device within 24 hours (Laboratoire Vivacy, Archamps, France), according to the internal procedures of the 2 companies:

- on a specific form attached to the observation book: "Serious Adverse Event Declaration Form",
- form to be sent by email within 24 hours after learning of the event, to the Proponent's Materiovigilance Manager at the following address: [[contact]](mailto:[contact])

12

If this is not possible, the information must be communicated by telephone within the same timeframe to the Vigilance Manager on [name].

The causal link with the medical device and/or its administration procedure must be suggested by the investigator (none, possible, probable, proven).

## **10-2. Immediate declaration to the National Agency for the Safety of Medicines and Health Products (ANSM)**

The sponsor shall immediately report to the competent authority the occurrence of any serious adverse event, serious adverse effect related to the use of the device and/or unexpected adverse effect related to the use of the device that an investigator reports to him. He also informs the other investigators participating in the study.

All information relating to a serious adverse event is integrated into the promoter's vigilance database. A summary is drawn up by the sponsor's pharmacovigilance unit in the form of CIOMS I.

The following main elements are identified on CIOMS I:

- a unique biomedical research identifier (EudraCT number),

[figure not shown]

- a coding of the event(s) considered serious, expected and unexpected, according to the dictionary of adverse effects terminology (MedDRA),
- imputability according to the investigator and imputability according to the sponsor.

The sponsor declares to the ANSM:

13

- All unexpected serious adverse effects likely to be due to the DM,
- All serious adverse events likely to be linked to the procedure for implementing the MD,
- Any safety data or new fact that could significantly modify the assessment of the benefit/risk ratio of the MD.

Usually do not require immediate reporting:

- Non-serious side effects,
- Adverse events considered unrelated to the MD or to the procedure for implementing the MD.

As defined in article R.1123-48 of the Public Health Code relating to vigilance in the context of biomedical research, any suspicion of an unexpected serious adverse effect and any serious adverse event that may be linked to the act of implementation of the medical device must be sent to the ANSM Medical Devices Clinical Monitoring and Evaluation unit.

